### Inclusion and exclusion criteria

This study will include and exclude participants following the criteria shown in
Table 2.

**Table 2. T2:** Inclusion and exclusion criteria.

Inclusion criteria	Exclusion criteria
• In Lusaka, only residents of Misisi compound and high SES residential areas, while in Harare, only patients who have been referred for a colonoscopy.	• This study will not include any individuals taking medication for type II diabetes.
• Only adults from high socio-economic status (i.e., living in detached houses with indoor flush toilets, tiled floors, separate kitchens with running water and indoor stoves, and own at least one vehicle) will be included in Harare and in the Zambian control group.	• Any contra-indication to study procedures including endoscopy, such as likely to cause problems with sedation (e.g., oropharyngeal anomaly, previous adverse reaction) or biopsy (e.g., bleeding diathesis).
• Participants of either sex will be included in the study.	• Pregnant or lactating.
• Participants aged between 18 and 65 years old.	• Currently taking any anticoagulants.
• Only participants who are able and willing to undergo HIV testing.	• Having renal failure or liver failure (any major organ system).
• Able and willing to give written, informed consent will be included.	• Any underlying condition, other than HIV, which in the opinion of the investigator would put the subject at undue risk of failing study completion or would interfere with analysis of study results.
	• Participants will be temporarily excluded from study procedures if they have had diarrhoea (by self-report) in the preceding month, and have taken antibiotics, non-steroidal anti-inflammatory drugs, and/or proton pump inhibitors in the preceding month until disqualifying condition has elapsed.

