### Study population

The initial study will be conducted in 80 adults from a population in Lusaka, Zambia, where our previous studies have demonstrated that EE is virtually ubiquitous in adults and children.
^
32
^ Additionally, 20 controls living in high socioeconomic status (SES) residential areas (Rhodes Park, Longacres, Kabulonga, Ibex Hill, Chelston, Avondale, Sunningdale, Roma, Chamba Valley, Lilayi, New Kasama and others) within Lusaka will be included. A further 20 patients attending for routine colonoscopy (for diagnostic purposes) in Harare, Zimbabwe will be enrolled for the antibiotic permeation study. As these participants will already be booked for colonoscopy they will be drawn from higher socio-economic groups.

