## Colonoscopy: Zimbabwe

An intravenous injection of a single dose of 600 mg benzylpenicillin will be given in patients presenting for colonoscopy, 10 – 15 minutes before the procedure. Luminal fluid from the right side of the colon will be aspirated between 20 and 40 mins after benzylpenicillin administration. This fluid will be centrifuged, stored, and shipped to Imperial College where the assays for the presence of benzylpenicillin, which will indicate reverse permeation, will be performed. This sub-study is directed at understanding whether the degree of barrier loss in environmental enteropathy is sufficient to permit leakage of antibiotics into the right colon. Penicillin was selected as it is a narrow-spectrum antibiotic which would not be expected to cause significant microbiome disruption in these healthy volunteers, which might be an ethical concern. A recent study
^
37
^ showed that antibiotic secretion into bile can modulate the microbiota during cardiac surgery, but this is a situation where gut hypoperfusion is well known to drive barrier failure. Such effects have not, to our knowledge, been shown in EE.

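### The Harare sub-study doses diagnostic colonoscopy patients before the colon is seen and states no rule for disease found there, so leakage through diseased right-colon mucosa could be read as enteropathy-related permeation

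*Protocol article*

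**What the plan says.** Study population sets the source and size of the Harare group: "A further 20 patients attending for routine colonoscopy (for diagnostic purposes) in Harare, Zimbabwe will be enrolled for the antibiotic permeation study". Table 2 (Inclusion and exclusion criteria) matches this, admitting "in Harare, only patients who have been referred for a colonoscopy", and Antibiotic analysis repeats the diagnostic purpose.

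Table 2 narrows entry further. Harare participants must be "Only adults from high socio-economic status", aged 18 to 65 and willing to be tested for HIV. Anticoagulant users and people with organ failure or a contraindication to the procedures are excluded. No colonic condition is named. The nearest criterion is a judgement clause: "Any underlying condition, other than HIV, which in the opinion of the investigator would put the subject at undue risk" of not completing the study, or which "would interfere with analysis of study results". Recent diarrhoea and recent use of certain drugs lead only to deferral.

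Colonoscopy: Zimbabwe has benzylpenicillin given 10 to 15 minutes before the procedure and right-colon fluid aspirated 20 to 40 minutes after the dose. The fluid is assayed "for the presence of benzylpenicillin, which will indicate reverse permeation". The section states that the sub-study is meant to show whether barrier loss in environmental enteropathy is enough to let antibiotics leak into the right colon. It justifies the choice of penicillin as a narrow-spectrum drug "which would not be expected to cause significant microbiome disruption in these healthy volunteers".

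**The concern.** There are two linked problems.

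First, the descriptions of the population conflict. People having a diagnostic colonoscopy are under investigation for a possible colonic problem. The rationale for the drug is argued for healthy volunteers, whom Table 2 does not enrol in Harare.

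Second, a positive sample has more than one possible source. Inflamed, ulcerated or bleeding mucosa at the sampled site could let drug into the lumen whatever the state of the patient's barrier elsewhere. The document takes presence of the drug as reverse permeation and aims the interpretation at environmental enteropathy, but states no way to tell the two sources apart. With 20 patients and no comparator group described in Harare, a few such samples could shape what Aim 5 is taken to show. If the colonoscopic findings are not captured in the study data, a later analysis may be unable to separate them.

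**Working it through.** **No figure to reproduce.** Sample size estimation covers the breath-test and permeability comparisons. It gives no power, precision or expected detection rate for the 20 Harare patients.

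**Which disease can be removed, and when**

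- Known or suspected before dosing: the investigator-opinion clause in Table 2 can exclude it, at the investigator's discretion.
- With recent diarrhoea: the temporary exclusion may defer entry. It joins diarrhoea to drug use with *and*, only postpones entry, and would not catch bleeding, tumour or colitis without diarrhoea.
- First seen at the procedure: the dose comes 10 to 15 minutes beforehand, so this disease cannot be screened out before dosing.

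**Timing of the sample.** The aspirate is taken 20 to 40 minutes after the dose. Relative to the start of the procedure, the earliest time is 20 − 15 = 5 minutes and the latest is 40 − 10 = 30 minutes. The endoscopist has reached the right colon by then, so its appearance can be known when the fluid is taken. No stated rule uses that information. Table 4 lists an antibiotic assay on colonic aspirates, one aspirate per procedure. The Statistical analysis plan section has no Harare-specific rule and anchors its comparisons on duodenal morphometry; duodenal biopsies are described for Zambia only.

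**Possible size.** The prevalence p of diseased right-colon mucosa among those enrolled is not in the documents, so it is assumed to be 5% to 40%. With n = 20:

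- Expected number affected = 20 × p
- Chance of at least one = 1 − (1 − p)^20

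| Assumed p | Expected of 20 | Chance of at least one |
|---|---|---|
| 5% | 1 | 1 − 0.95^20 = 0.64 |
| 10% | 2 | 1 − 0.90^20 = 0.88 |
| 20% | 4 | 1 − 0.80^20 = 0.99 |
| 40% | 8 | 1 − 0.60^20 > 0.99 |

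**Effect on the detection rate.** If a fraction q of diseased colons leak, they add p × q to the overall detection rate. At p = 20% this is 10% when q = 0.5 and 20% when q = 1. The ceiling, at q = 1, is p itself, so this step only returns the assumption and is not an estimate.

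**The case against.** Four points can be made against this, and most of them limit it.

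- **Entry is not open.** A reader might infer that any referred patient gets in. Table 2 does not support that. The socio-economic, age, anticoagulant and organ-failure criteria apply, and the investigator clause can cover known colitis or tumour. This stands. Only disease first found at the procedure clearly escapes.
- **The healthy-volunteer phrase is not an analysis rule.** It sits in the ethical argument for a narrow-spectrum drug, and no sample is counted differently because of it. This stands. The phrase is a contradiction to correct and does not cause the attribution problem.
- **The readout is not wrong in itself.** Aim 5 asks whether intravenous antibiotics reach the gut lumen in quantities that could modulate the microbiota. Drug that crosses a diseased colon has permeated in that sense. This also stands. The difficulty comes from directing the result at barrier loss in environmental enteropathy.
- **The missing rule may lie elsewhere.** This is a condensed article, and handling of colonoscopic findings could be in the full protocol or an analysis plan. This stands in part, so the claim is that misreading could happen and not that it will. However, the article itself fixes the population, the timing of the dose and the meaning of a positive sample, and together these create the ambiguity.

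A reader might also infer that leakage in 5% to 40% of patients would be due entirely to colonic disease. That needs both an assumed prevalence and the further assumption that every diseased colon leaks and no other does. The documents support neither.

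**Conclusion.** The point holds in a limited form. The descriptions of the Harare population contradict each other. As written, the plan also has no stated means of separating leakage through diseased or bleeding right-colon mucosa, first seen at the procedure, from the permeation it interprets in terms of enteropathy.

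The size is unknown. On the assumed prevalence of 5% to 40%, at least one affected patient among 20 is more likely than not (64% to over 99%), and 1 to 8 would be expected. These figures treat patients as independent and rest wholly on the assumed range. How many affected patients would yield a positive sample is not known either.

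This is distinct from the absence of an enteropathy group or enteropathy measure in Harare. Separating out diseased mucosa removes one competing explanation. It does not by itself allow a positive sample to be attributed to enteropathy.

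**What to change.** 1. For each Harare patient, record the appearance of the right colon from the colonoscopy report.
2. Base the main Aim 5 readout on patients with macroscopically normal, non-bleeding right-colon mucosa. Fix this definition before the assay results are seen.
3. Report the remaining patients as a separate descriptive group.
4. Reconcile the healthy-volunteer wording in Colonoscopy: Zimbabwe with Study population, Table 2 and Antibiotic analysis, and restate the rationale for the population actually enrolled.

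The cost is protocol wording and one data field from a report that the diagnostic procedure should already produce. The downside is a main readout on fewer than 20 patients: on the assumed range, 20 − 1 = 19 down to 20 − 8 = 12 would be expected to remain. If none of them had detectable drug, the one-sided 95% upper limit for the detection rate, 1 − 0.05^(1/n), would be 14.6% at n = 19 and 22.1% at n = 12, against 13.9% at n = 20. That loss of precision is acceptable for a readout with one fewer competing explanation.

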*Salmonella typhimurium*-specific IL-8 responses in the children at 18 months. Furthermore, children who received water, sanitation, and hygiene (WASH) interventions demonstrated higher inducible LPS-specific myeloperoxidase (MPO) levels compared to those who did not receive such interventions. These findings underscore the complex interplay between the immune system, SAM, and EE. Further research is needed to better understand and differentiate the immune responses in SAM and EE, across both children and adults.

Both SAM and the antibiotic treatments recommended for children admitted to hospital with SAM also affect the gut microbiome, the composition of which is associated with lower bacterial diversity and maturity, which fail to persistently recover with standard nutritional therapies.
^
21
^ Characterization of the small intestinal microbiome in children is challenging due to the invasiveness of endoscopy procedures. Some studies showed through culture methods that small intestinal bacterial overgrowth (SIBO) is associated with stunting in children from Bangladesh,
^
22
^ Central African Republic and Madagascar. These studies also provided the first evidence, using 16s sequencing, of decompartmentalization of the microbiome along the GI tract in stunted growth and EE
^
23
^
^,^
^
24
^ and demonstrated a loss of carbohydrate-metabolising microbes in the small intestine.
^
25
^ These findings suggest that small intestinal microbes contribute to the pathophysiology of stunting however, these findings are relatively novel and need validation with different cohorts. There is a need to take a holistic approach to understanding the impact of undernutrition and EE on gut physiology across the whole gastrointestinal tract, which means developing tools for assessing multiple domains
^
26
^ of gut function (

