### Study aims

Aim 1: Evaluate a novel portfolio of stable isotope-based tools for evaluating carbohydrate and protein digestion and amino acid absorption.

Aim 2: Test a novel non-invasive fluorescence sensor-based tool for real-time evaluation of gut permeability.

Aim 3: Characterise the microbiome and metabolome across well characterised and novel physiological sites (duodenal aspirate, duodenal mucus, duodenal tissue, stool, plasma, urine).

Aim 4: Quantify systemic and intestinal inflammation using established biomarkers of EE, immune cell phenotyping, epithelial PRR expression, and in vitro epithelial barrier models.

Aim 5: Determine if antibiotics, given intravenously, permeate into the gut lumen in sufficient quantities to modulate the microbiota.

All of these will be correlated with histological mucosal morphometry, lactulose permeation, and established biomarkers of EE.

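### The temporary-exclusion rule in Table 2 joins diarrhoea and recent drug use with *and*, so read literally it admits people with either exposure alone

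*Protocol article*

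**What the plan says.** Table 2 of the Protocol article (Inclusion and exclusion criteria) ends its exclusion column with a temporary deferral that applies to participants "if they have had diarrhoea (by self-report) in the preceding month, and have taken antibiotics, non-steroidal anti-inflammatory drugs, and/or proton pump inhibitors". Its first limb reads "Participants will be temporarily excluded from study procedures if they have had diarrhoea (by self-report) in the preceding month". Its second limb follows directly: "and have taken antibiotics, non-steroidal anti-inflammatory drugs, and/or proton pump inhibitors in the preceding month until disqualifying condition has elapsed". The *and/or* in the second limb works only inside the list of drugs. The two limbs are joined by a plain *and*.

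No other part of the article restates the rule. The nearest safeguard is another bullet in the same column: "Any underlying condition, other than HIV, which in the opinion of the investigator would put the subject at undue risk of failing study completion". That bullet goes on to cover interference with the analysis of results, but it remains limited to an underlying condition. It names neither recent drug use nor a diarrhoeal episode that has resolved.

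The measurements that the rule would protect are central to the study. Aim 2 is "Test a novel non-invasive fluorescence sensor-based tool for real-time evaluation of gut permeability" and Aim 3 is "Characterise the microbiome and metabolome across well characterised and novel physiological sites". Aim 4 quantifies systemic and intestinal inflammation.

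**The concern.** A temporary exclusion of this kind exists to keep recent exposures out of the measurements. If it takes effect only when two exposures coincide, most people with one of them pass through. The results could then contain shifts in microbiota, permeability or inflammation markers that reflect a recent drug or a recent illness rather than enteropathy.

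The Statistical analysis plan section compares all data with duodenal morphometry, in order to validate the new tools for sensitivity to EE severity within the cohort. An exposure that moves a marker without a matching change in morphometry could weaken a real correlation. One that moves both could create a spurious correlation. There is also a practical problem: two screening staff could apply the sentence differently, and a later reader could not tell which cohort was enrolled.

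**Working it through.** There is no stated figure to reproduce, because the point concerns the logic of one sentence. Let A be self-reported diarrhoea in the preceding month and B be use of any listed drug in the preceding month.

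| Exposure | Text as written (A and B) | Either/or reading (A or B) |
|---|---|---|
| A and B | deferred | deferred |
| A only | admitted | deferred |
| B only | admitted | deferred |
| neither | admitted | admitted |

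**Which reading was meant.** The one-month window is stated separately for each limb, which would be redundant in a single joint condition. The closing phrase refers to one disqualifying condition, in the singular. Both features suggest that each exposure was meant to defer by itself.

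**What the document supports on consequences.** For antibiotics and the microbiome, the Introduction says that "the antibiotic treatments recommended for children admitted to hospital with SAM also affect the gut microbiome". That statement concerns children with severe acute malnutrition. The article gives no data on PPIs and the microbiota, or on NSAIDs or diarrhoea and permeability. For these, the only pointer is that the protocol chose to list them.

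**Illustrative size.** The article gives 80 adults ("The initial study will be conducted in 80 adults from a population in Lusaka, Zambia") and no prevalences. I assume d for diarrhoea and g for drug use among those screened, in three paired scenarios. The number with exactly one exposure among 80 enrolled under the literal rule is

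80 × [P(or) − P(and)] / [1 − P(and)],

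where the denominator is the share not deferred.

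*Independence:* P(and) = dg and P(or) = d + g − dg.
- d = 5%, g = 10%: P(and) = 0.005, P(or) = 0.145; 80 × 0.140/0.995 = 11.3
- d = 10%, g = 20%: P(and) = 0.020, P(or) = 0.280; 80 × 0.260/0.980 = 21.2
- d = 15%, g = 30%: P(and) = 0.045, P(or) = 0.405; 80 × 0.360/0.955 = 30.2

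*Complete overlap* (everyone with diarrhoea also took a listed drug): P(and) = d and P(or) = g.
- 5%, 10%: 80 × 0.05/0.95 = 4.2
- 10%, 20%: 80 × 0.10/0.90 = 8.9
- 15%, 30%: 80 × 0.15/0.85 = 14.1

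Under independence, the literal rule defers 0.5% to 4.5% of those screened and the either/or rule 14.5% to 40.5%. The overlap figures depend on the pairing. With d = 5% and g = 30%, complete overlap gives 80 × 0.25/0.95 = 21.1. With equal prevalences it gives none.

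**The case against.** The strongest reply is that this is loose drafting and not a design decision. The comma, the repeated window and the singular closing phrase all point to two separate grounds for deferral, and trained staff may well apply them that way. Nothing in the document shows that anyone was screened under the literal reading. That stands, and it limits what can be claimed about the enrolled cohort. It does not rescue the text, which is an operative eligibility rule that says something different from its apparent purpose.

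A second reply is that the investigator-opinion bullet gives some cover. It may catch a person whose drug use or diarrhoea comes from an underlying illness. It would not reliably catch a short antibiotic course or a resolved episode.

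A third reply is that diarrhoea and drug use are probably not independent, since one may prompt the other. Positive association narrows the gap between the two readings, which is why the complete-overlap figures are shown beside those for independence.

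A reader might also infer that drug use differs between Misisi residents and the high-SES controls, so that the contrast between them is biased. The document gives no drug use by group and does not support that step. Its stated validation is also a comparison with morphometry within the cohort, not mainly a contrast between groups.

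**Conclusion.** The point holds as a wording error in a stated eligibility rule. Taken literally, the bullet defers only people with both diarrhoea and a listed drug, and it admits those with either alone. The consequence is possible confounding of the Aim 2 to 4 measures and of their correlation with morphometry. It is not a demonstrated bias, and its size and direction cannot be derived from the document.

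The counts of roughly 4 to 14 of 80 (complete overlap) and 11 to 30 of 80 (independence) rest wholly on assumed prevalences paired as above. They show that the number need not be trivial and should not be read as an estimate for this cohort. Confidence is high on the grammar and low on the effect.

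**What to change.** Reword the bullet so that the exposures are joined by *or*: diarrhoea by self-report, or antibiotics, or NSAIDs, or PPIs in the preceding month, with the protocol's own one-month window unchanged. If the combination really was intended, say so explicitly and give the reason. In either case, reconcile the text with how screening is actually done.

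If any participant was enrolled with a single exposure, flag that person in the dataset and repeat the microbiome, permeability and inflammation analyses without those flagged, as a sensitivity analysis.

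The cost is a short amendment and some enrolments deferred until the window has passed. The sensitivity analysis would lose some precision if many people are flagged.

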## Protocol

### Screening and initial assessment

Participants will be consented for HIV testing as part of the consent process, before enrolment. Consenting for HIV testing and communication of results will be performed by an experienced and fully trained team of research staff and counsellors. HIV counselling and testing have been performed by this team both as part of standard medical care in the Misisi clinic and as part of the routine research process in our recent studies for over 15 years.
^
10
^
^,^
^
35
^ Likewise, HIV counselling and testing are standard of care in Zimbabwean health care facilities. HIV test results will be given in person and confidence in the clinic of recruitment. Participants found to be HIV seropositive will be allowed to discuss their results and management in more detail. With their consent, they will be referred to HIV specialists for further investigation and management including anti-retroviral therapy per Ministry of Health guidelines and procedures in both Zambia and Zimbabwe. Test results remain confidential and will not be shared with anyone outside of the study team without the participant’s explicit consent.

